| Tertiary | 
1. Do psychiatric, personality, trauma and social support factors at baseline (social support, trauma exposure, anxiety, age, gender, education, neuroticism, past and current psychiatric status, immune and hormone function) influence (i.e., moderate) levels of symptoms (PTSD or MD) psychological distress and wellbeing at follow-up?
 
2. Do changes in resilience-related factors (rumination, responses to intrusions, concrete thinking, resilience appraisals, practice of iCT-R/Mind-Online tools) mediate symptom levels of PTSD and MD at one year follow-up with iCT-R and Mind-Online?
 
3. Do changes in resilience-related factors (rumination, responses to intrusions, concrete thinking, resilience appraisals, practice of iCT-R/Mind-Online tools) mediate symptom levels of PTSD and MD at two year follow-up with iCT-R and Mind-Online?
 | 
1.
 
Neuroticism: Eysenck Personality Questionnaire, Neuroticism subscale (EPQ)
 
Social Support (SS)adapted from 36
 
Age, gender, education: Demographic Questionnaire (unpublished)
 
Psychological Distress: GHQ
 
Wellbeing: WEMWBS
 
Immune function: CRP
 
Hormone function: Cortisol
 
1., 2., and 3
 
Past & Current Psychiatric Status: Structured Clinical Interview for DSM-V
 
Symptoms PTSD: PCL-5
 
Symptoms Depression: PHQ-9
 
Anxiety: GAD-7
 
Trauma Exposure: Trauma Screener (unpublished)
 
2. and 3.
 
Rumination: Ruminative Response Scale (Brooding Subscale)
 
Intrusions: Response to Intrusions Questionnaire (RIQ), short version
 
Duration, Frequency, Distress Linked to Intrusions (unpublished)
 
Concrete Thinking: Concrete & Abstract Thinking (unpublished)
 
Practice iCT-R/Mind Online tools (unpublished)
 
Resilience: CD-RISC & Resilience Scale (Wagnild & Young)
 |

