|                      |                                                                                                                                                                                      |                                                                                                                                                                                                                                                                                             |
|----------------------|--------------------------------------------------------------------------------------------------------------------------------------------------------------------------------------|---------------------------------------------------------------------------------------------------------------------------------------------------------------------------------------------------------------------------------------------------------------------------------------------|
|                      | 4. Does concrete thinking, practice of tools and responses to intrusions at 6 months predict diagnoses and levels of PTSD and depression symptoms at one year?                       | 4.
Intrusions: Response to Intrusions Questionnaire (RIQ)  , short version
Duration, Frequency, Distress Linked to Intrusions (unpublished)
Concrete Thinking: Concrete & Abstract Thinking (unpublished)
Practice iCT-R/Mind Online tools (unpublished) |
| Treatment conditions | 1. Supported Internet-delivered cognitive training for resilience (iCT-R)
2. Supported Internet-delivered mental health education (Mind-Online)
3. 24 months standard practice |                                                                                                                                                                                                                                                                                             |

35  
36

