| Tertiary Objectives

1. Do psychiatric, personality, trauma and social support factors at baseline (social support, trauma exposure, anxiety, age, gender, education, neuroticism, past and current psychiatric status, immune function) influence (i.e., moderate) levels of symptoms (PTSD or MD) psychological distress and wellbeing at follow-up?

2. Do changes in resilience-related factors (rumination, responses to intrusions, concrete thinking, resilience appraisals, practice of iCT-R/Mind-Online tools) mediate symptom levels of PTSD and MD at one year follow-up with iCT-R and Mind-Online?

3. Do changes in resilience-related factors (rumination, responses to intrusions, concrete thinking, resilience appraisals, practice of iCT-R/Mind-Online tools) mediate symptom levels of PTSD and MD at two year follow-up with iCT-R and Mind-Online?

4. Does concrete thinking, practice of tools and responses to intrusions at 6 months predict diagnoses and levels of PTSD and depression symptoms at one year? | 1.
Neuroticism: Eysenck Personality Questionnaire, Neuroticism subscale (EPQ) 
Social Support (SS) adapted from 36
Age, gender, education: Demographic Questionnaire (unpublished)
Psychological Distress: GHQ 
Wellbeing: WEMWBS 
Immune function: CRP
Hormone function: Cortisol

1., 2., 3 and 4
Past & Current Psychiatric Status: Structured Clinical Interview for DSM-V 
Symptoms PTSD: PCL-5 
Symptoms Depression: PHQ-9 
Anxiety: GAD-7 
Trauma Exposure: Trauma Screener (unpublished)

2. and 3.
Rumination: Ruminative Response Scale  (Brooding Subscale)
Intrusions: Response to Intrusions Questionnaire (RIQ)  , short version
Duration, Frequency, Distress Linked to Intrusions (unpublished)
Concrete Thinking: Concrete & Abstract Thinking (unpublished)
Practice iCT-R/Mind Online tools (unpublished)
Resilience: CD-RISC  & Resilience | 1.
Baseline
6 weeks
52 weeks
104 weeks

2. and 3.
Baseline
6 weeks
52 weeks
104 weeks

4.
Baseline
6 weeks
24 weeks |

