## **Objectives**

The primary trial objective is to evaluate whether the newly developed iCT-R intervention is more effective than the existing Mind-Online intervention at 1-year and at 2-years follow-up with regards to PTSD and MDD diagnoses.

Secondary trial objectives are to evaluate the efficacy of iCT-R compared to Mind-Online at 1-year and at 2-year follow-up with regards to secondary outcomes, such as resilience and well-being measures, as well as general health measures, and in terms of health economic costs. Furthermore, the effects of iCT-R versus Mind-Online on immune and hormone function will be compared at post-intervention.

Tertiary trial objectives are to investigate whether risk factors and predictors at baseline, such as level of social support, trauma exposure, demographic data, neuroticism as a personality factor, level of concrete thinking, frequency, duration, and distress with regards to intrusive memories influence any effects of iCT-R on PTSD and MDD diagnoses, psychological distress, and well-being at 1-year follow-up.

Further tertiary objectives are to investigate whether changes from baseline to post-intervention in resilience factors, such as rumination, responses to intrusive memories, level of concrete thinking, and resilience appraisals, predict PTSD and MDD diagnoses at 1-year follow-up in the iCT-R intervention group.

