Linear mixed effects models are specified for these continuous outcome measures. Intervention condition (categorical; iCT-R versus Mind-Online versus Standard Practice; level 2) and the interaction between intervention time (categorical; post-intervention, 1-year-follow-up, 2-years-follow-up once completed; level 1) are specified as fixed effects predictors in the models.

Baseline values for the respective secondary outcome are added as covariate in these models together with PTSD and MDD symptom severity at baseline, and randomisation factors.

Adjusted/ estimated mean differences and Cohen's d's with standard deviation at baseline in the denominator are reported in tables for continuous outcomes for the intervention effects from results of linear mixed effects models.

The health economic analyses will be conducted and reported by [name] and and hormone and immune function are tested by collaborators and are therefore not part of this statistical analysis plan. A plan for the health economic and hormone and immune function analyses will be agreed.

Analyses of the tertiary trial objectives:

In order to investigate whether risk factors and predictors at baseline, such as level of social support, trauma exposure, demographic data, past and current comorbidities, neuroticism as a personality factor, level of concrete thinking, and frequency/ duration/ distress with regards to intrusive memories, influence any iCT-R intervention effects on PTSD or MDD diagnoses, psychological distress, and well-being at 1-year follow-up, a mixed effects model for each of the outcomes, PTSD and MDD diagnoses, psychological distress, and well-being, is specified with baseline scores of PTSD or MDD symptom severity or psychological distress or well-being as covariate. The main effects of the respective baseline predictors (time-invariant covariates) and the two-way interactions between each of those baseline predictors and time (categorical: post-intervention, 1-year follow-up; level 1) will be analysed.

Again, Maximum Likelihood is used if the assumption of normality of the residuals of the outcomes is fulfilled. An unstructured variance-covariance structure matrix is used, all significance tests are carried out on a  $p < .05$  level, two-sided, and confidence intervals are reported at the 95% level.

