In case of any significant interaction effects between time and baseline moderators, simple slope analyses are carried out to investigate the direction of any moderation effects.

Further tertiary trial objectives to investigate whether changes (decrease) in process measures, such as rumination, intrusive memories, and increases in concrete thinking, from baseline to post-intervention in the iCT-R condition predict lack of PTSD or MDD diagnoses

[name], [name], [name], [name], [name], [name], [name], [name], [name], [name], [name], & [name] Cognitive resilience training to prevent PTSD and MDD in paramedics: A randomised controlled trial.

(versus presence of PTSD or MDD diagnoses) at 1-year follow-up are analysed using logistic regressions with difference scores from pre to post for the process measures and baseline scores of PTSD or MDD symptom severity as covariate.

CACE analysis:

A complier-average causal effect analysis (CACE) is used to test the influence of compliance on the intent-to-treat intervention effect of the primary trial objectives/ analyses. Magnitude of compliance will be defined as 1) number of online modules completed during the intervention, and 2) practice of tools. Based on these variables, trajectories of compliance are determined. CACE will then be compared with the intent-to-treat intervention effects resulting from the primary analyses and the results will be reported.

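### The SAP's process-change analyses, and the PTSD/MD part of its moderator analyses, use yes/no diagnoses at 1 year where the protocol asks about symptom levels, for mediators at one and two years in both online arms

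*Combined protocol and SAP*

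**What the plan says.** **Protocol.** In the Synopsis and section 5, tertiary objective 2 asks whether changes in process factors such as rumination, concrete thinking and resilience appraisals "mediate symptom levels of PTSD and MD at one year follow-up with iCT-R and Mind-Online". Objective 3 asks whether they "mediate symptom levels of PTSD and MD at two year follow-up with iCT-R and Mind-Online". Objective 1 asks whether baseline factors "influence (i.e., moderate) levels of symptoms (PTSD or MD) psychological distress and wellbeing at follow-up". PCL-5 and PHQ-9 are the symptom measures listed, and Appendix B schedules both at every assessment, including weeks 52 and 104.

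**SAP.** Section 2.2 (Objectives) recasts the mediator question: do baseline-to-post changes "predict PTSD and MDD diagnoses at 1-year follow-up in the iCT-R intervention group"? Section 6.2 (Analysis Methods) gives the method. The predictors of having or not having a diagnosis "at 1-year follow-up are analysed using logistic regressions with difference scores from pre to post for the process measures", with baseline severity as covariate. For moderators, section 6.2 asks whether baseline factors "influence any iCT-R intervention effects on PTSD or MDD diagnoses, psychological distress, and well-being at 1-year follow-up", with time taken as post-intervention and 1 year. Section 3.7 repeats both.

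In these tertiary models PTSD and MDD symptom severity enters only as a baseline covariate. The SAP does model PCL-5 and PHQ-9 as outcomes for the primary objective, but those models contain no moderators or process-change scores. The SAP's change table has no entry, because this is the first issue.

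**The concern.** For the mediator objectives the SAP changes three things at once: the outcome (symptom level to diagnosis), the time points (two to one) and the arms (two to one). For the moderator objective it changes the PTSD/MD outcome and names only 1 year. None of this is explained, although the continuous scores will have been collected.

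The training was built to change rumination and resilience appraisals, so the process analysis is the trial's test of its own mechanism. A logistic regression on few events can miss a modest association. A non-significant result could then be read as evidence against the mechanism when the analysis had little chance of detecting it.

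**Working it through.** **1. The plan's own sample size.** Inputs (protocol 11.2): 25% against 12.5%, power 80%, α 0.05; two-sided per SAP 4.1.

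n per arm = [1.96·√(2·0.1875·0.8125) + 0.8416·√(0.25·0.75 + 0.125·0.875)]² / 0.125² = 151.9, so 152 per arm and 304 in total. Three arms give 456, and 456/0.80 = 570, or 190 per arm. The plan's figures reproduce.

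**2. Expected events.** SAP 3.5 gives 1-year rates in the total sample of 8.7% (PTSD) and 15.8% (depression). Rates by arm are not given.

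| Model and n | PTSD events | MDD events |
|---|---|---|
| Process regressions, iCT-R, 152 | 13.2 | 24.0 |
| Same, all 190 assessed | 16.5 | 30.0 |
| Same, 152, iCT-R at half the rate of the other arms | 7.9 | 14.4 |
| Moderator model, all arms, 456 | 39.7 | 72.0 |

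For the half-rate row, a pooled rate p implies an iCT-R rate of (3p/2.5)/2. That is 5.22% for PTSD and 9.48% for MDD. With one change score plus baseline severity, the process regression has 13.2/2 = 6.6 PTSD events per term and 24.0/2 = 12.0 MDD events per term.

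**3. Information kept by a yes/no outcome.** Assume that diagnosis is a cut at prevalence p on a latent normal severity scale. Relative efficiency is φ(z)²/[p(1−p)], where z is the cut-off.

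- PTSD: p = 0.087, z = 1.36, φ = 0.158; 0.0251/0.0794 = 0.32.
- MDD: p = 0.158, z = 1.00, φ = 0.241; 0.0582/0.1330 = 0.44.

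So about 68% and 56% of the information is lost.

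**4. Power over a range of effects.** The documents give no effect size for this analysis, so the correlation r between process change and later severity is assumed. Simulation used n = 152, 1,500 runs per setting and a baseline covariate with coefficient 0.4, comparing linear regression with a logistic likelihood-ratio test.

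| r | Continuous score | PTSD diagnosis | MDD diagnosis |
|---|---|---|---|
| 0.2 | 78% | 30% | 40% |
| 0.3 | 99% | 60% | 73% |
| 0.4 | 100% | 83% | 95% |

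A Fisher-z approximation without the covariate gives 70/28/37%, 96/55/69% and above 99/80/91%, the same pattern.

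**5. Effect of restoring Mind-Online.** By the same approximation, r = 0.226 gives 80% power for a continuous score with n = 152. With both online arms (n = 304) and the same association in each, it gives 98%.

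**The case against.** Several points against a broader criticism stand.

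- **A reader might apply the 13 PTSD events to the moderator analysis too.** The iCT-R restriction is stated only for the process regressions. The moderator model is not stated to be limited to one arm, and across all arms it would have about 40 PTSD and 72 MDD events.
- **A reader might infer that every moderator outcome was replaced.** Psychological distress and well-being remain; only the PTSD/MD symptom part was swapped.
- **A reader might conclude that most of the power is lost.** That depends on an effect size the documents do not give. In the simulation, power falls by more than half for PTSD at r = 0.2, but by less than half at 0.3 and above.
- **A reader might say that the two-year question is dropped.** SAP 3.5 says in general that two-year data will be added to the 1-year outcome models. This provision is unclear for the tertiary objectives: 3.7 ties the two-year time point to the primary and secondary objectives, the tertiary text names only 1 year, and a single-time-point logistic regression has no stated way to take in a second. That shows a missing specification, not a decision to omit.
- **Diagnoses are not foreign to the tertiary aims.** Objective 4 asks whether 6-month measures "predict diagnoses and levels of PTSD and depression symptoms at one year". But it names both outcomes, and it is a different question from objectives 1 to 3.

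Three further cautions are fair. SAP 6.2 does not say that the change scores enter one joint model. If its wording means either diagnosis, events would number roughly 24 to 37 (152 × 15.8% to 152 × 24.5%). The SCID is a separate interview by a blinded assessor, so treating it as a cut on the questionnaire scale is a simplification.

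Finally, these analyses are exploratory. No primary or secondary conclusion depends on them.

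**Conclusion.** The mismatch is real and should be corrected. For objectives 2 and 3, the SAP's tertiary text departs from the protocol in outcome, time points and arms. For objective 1 it departs in the PTSD/MD outcome, and it names only 1 year for the follow-up. No reason is given for any of these changes.

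The iCT-R process regressions would rest on about 13 PTSD and 24 MDD events, with ranges of about 8 to 17 and 14 to 30. These counts apply pooled rates to planned numbers, so they are approximate. Under the latent-normal assumption, diagnosis keeps about a third (PTSD) to somewhat under a half (MDD) of the information. In power terms the loss is severe for small effects and modest for large ones. The supportable conclusion is that a null process result would be uninformative about small effects, not that the analysis is bound to fail.

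**What to change.** In SAP 2.2, 3.7 and 6.2:

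- Make PCL-5 and PHQ-9 scores at 1 year, and at 2 years once complete, the outcomes of the process-change analyses. Run them in iCT-R and Mind-Online, as the protocol states.
- Use the same outcomes and time points for the PTSD/MD part of the moderator analyses. Leave distress and well-being in place as moderator outcomes.
- Fit linear or linear mixed models adjusted for the baseline score.
- Keep the logistic models on diagnoses as supportive, reported with their event counts.

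The cost is SAP wording and a few extra models on data already collected. The trial schedule does not change.

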### 11.2 The Number of Participants

We plan to recruit 570 participants.

The risk of student paramedics developing full syndromal PTSD and MD over two years without intervention is 10% (1), and 25% if subsyndromal PTSD and MD that cause significant distress are included. We predict that our intervention will reduce the relative risk by 50%. Setting power at 80%,  $\alpha=.05$  and hypothesizing a reduction of relative risk of 50% gives an odds ratio of 0.429, which requires a total sample size of N=304 to show a risk reduction of 50% between the active and placebo intervention. Thus, each condition would require N=152. Since we have a third condition (no-training control), the total sample size required would be N=456. Allowing for a 20% rate of attrition, we will require a total sample size of N=570.

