## **BACKGROUND AND OBJECTIVES**

### **Background and rationale**

Emergency workers are at risk for major depression (MD) and posttraumatic stress disorder (PTSD), and an associated risk of poor physical health due to the nature of their work.[1] To date, interventions aimed at reducing risk of mental ill health in this population have been unsuccessful. Randomised controlled trials (RCT) found that trauma risk management, a peer support system widely available to the police and ambulance services in England, [2] critical incident stress debriefing widely used by UK fire-services, [3] and the charity Mind's six-session group-based resilience intervention had no effect on resilience or rates of mental ill health [4]. More effective preventative interventions for emergency workers are urgently needed.

Established interventions may have been unsuccessful because they fail to target predictors of mental ill health and are offered to emergency workers after rather than before repeated exposure to the stresses linked to their work. Moreover, cognitive strategies that could help them cope with characteristic stressors are not included as part of the training. For example, our and others' research has demonstrated that exposure to trauma or stressful scenarios through imagery reduces anxiety for police officers and other at risk populations. [5, 6] Development of more effective interventions requires identification of predictors of mental disorders and an understanding of how to modify them.

In a series of experimental and prospective studies, we identified two cognitive factors that are robust predictors of poor mental health in emergency workers: rumination (repetitive negative thinking) and resilience appraisals. Those who reported ruminative thoughts during critical incidents were more likely to experience poor levels of coping. [7] Adaptive appraisals during analogue trauma led to more successful attempts to regulate

emotions and fewer PTSD symptoms. [8] Our large-scale prospective study of newly recruited paramedics investigated predictors of PTSD and MD derived from cognitive theories of PTSD and depression. [1] Rumination at the start of paramedic training uniquely predicted PTSD; low resilience uniquely predicted an episode of MD.

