#### **Timing of Final Analysis**

Originally, as stated in the published trial protocol ([name] et al., 2018), we had planned to analyse the trial data once the trial was finished at two year follow-up. However, the outbreak of the Covid pandemic may have added additional risk to the mental health of emergency workers and therefore, if iCT-R leads to improvement in emergency workers' mental health compared to Mind-Online or Standard Treatment, it would be beneficial to roll out the intervention as soon as possible. It has been discussed and agreed with the Trial Steering Committee that data could be analysed early, namely after completion of the 1-year follow-up period, if rates of PTSD and MDD diagnoses in the total sample at 1-year follow-up are higher than expected. At 1 year follow-up, in the total sample, rates of PTSD are 8.7% compared to 8.3% in non-intervention studies of this population [1] and the general population rate of 3%. Rates of depression are 15.8% compared to 10.6% in non-intervention longitudinal studies of this population [1] and the general population rate of 10.3%. Since

there are higher than expected rates of PTSD and MDD diagnoses at 1-year follow-up in the total sample we now plan to analyse data at 1-year follow-up. Two-year follow-up data (including sub-thresholds) will be analysed by including them into the 1-year outcome models once they have been completed.

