Estimated/ adjusted mean differences and Cohen's d's are reported for continuous outcomes. Cohen's d's with standard deviation at baseline in the denominator are reported for the treatment effects from results of linear mixed effects models. Estimated/ adjusted odds ratios are reported for dichotomous outcomes together with absolute values. Confidence intervals are reported at the 95% level, two-sided.

Tertiary trial objectives to investigate any influences of baseline risk factors and predictors on iCT-R intervention effects on outcomes, such as PTSD or MDD diagnoses, psychological distress, or well-being, are tested using linear and logistic mixed effects models using the same analysis principles as for the primary and secondary trial objectives. The main effects of the respective baseline risk factors and predictors (time-invariant covariates) and the two-way interactions between each of those baseline predictors and time (categorical: post-intervention, 1-year follow-up; level 1) are analysed. Baseline scores of PTSD or MDD symptom severity, or psychological distress, or well-being are used as covariates.

In case of any significant interaction effects between time and baseline moderators, simple slope analyses are carried out to investigate the direction of any moderation effects. Further tertiary trial objectives to investigate whether changes in process measures, such as rumination, intrusive memories, and concrete thinking, from baseline to post-intervention in the iCT-R condition predict PTSD and MDD diagnoses at 1-year follow-up will be analysed using logistic regressions with difference scores from pre to post for the process measures and baseline scores of PTSD or MDD symptom severity as covariate.

CACE and sensitivity analyses are conducted for the primary trial objectives.

Results are reported in APA format.

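### The iCT-R process models use pre-to-post change scores without the process measure's own baseline level, so the change effect is biased to the extent that baseline level itself predicts diagnosis

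*Combined protocol and SAP*

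**What the plan says.** The SAP describes the process analysis twice. Statistical Analysis Outline specifies "logistic regressions with difference scores from pre to post for the process measures", with baseline PTSD or MDD symptom severity as the covariate. Analysis Methods (tertiary objectives) repeats this: "logistic regressions with difference scores from pre to post for the process measures and baseline scores of PTSD or MDD symptom severity as covariate". The question is whether changes "from baseline to post-intervention in the iCT-R condition predict lack of PTSD or MDD diagnoses" at 1 year, so the analysis uses one arm. The measures named there are rumination, intrusive memories and concrete thinking; SAP Objectives also lists resilience appraisals.

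Neither section enters the baseline level of the process measure. The secondary-outcome models in the same section do the equivalent: "Baseline values for the respective secondary outcome are added as covariate in these models". That sentence does not extend to the process models, and no reason is given for the difference.

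The SAP's Background and rationale reports from the sponsor's earlier prospective study: "Rumination at the start of paramedic training uniquely predicted PTSD; low resilience uniquely predicted an episode of MD". No effect size is given.

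**The concern.** A coefficient on (post − pre) alone gives post and pre equal and opposite weights. At any fixed post-training level, higher baseline rumination is then made to lower the risk of a diagnosis. If baseline level carries risk that change does not account for, the model has nowhere to put it except the change coefficient. People who start high tend to fall most (regression to the mean) while remaining at higher risk, so the misplaced effect works against the hypothesis.

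This is the SAP's specified test of whether shifting the processes that iCT-R targets goes with fewer diagnoses. A real association could be understated. In the extreme, improvement could appear to predict illness.

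**Working it through.** **Participants and events.** The documents give no figure for this analysis, so there is none to reproduce. The number available follows from the trial sample size: 25% against 12.5% gives OR = (0.125/0.875)/(0.25/0.75) = 0.429, 152 per arm, 3 × 152 = 456, and 456/0.8 = 570, as stated. The iCT-R arm is 570/3 = 190 randomised, or 152 after 20% attrition. At the total-sample 1-year rates in the SAP's Timing of Final Analysis (PTSD 8.7%, MDD 15.8%), that is 152 × 0.087 ≈ 13 PTSD events and 152 × 0.158 ≈ 24 MDD events.

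**Assumed inputs (none is in the documents).** r is the baseline–post correlation, k the post/pre SD ratio, and q the correlation of baseline process score with baseline symptom score. Post scores relate to baseline symptoms only through the baseline process score. Effects are log-odds per baseline SD of the process measure.

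**Algebra.** Let D = post − pre, B = baseline process level and S = baseline symptoms, with true log-odds b·D + c·B + s·S. Leaving out B gives a coefficient on D of approximately b + c·δ, where

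δ = (rk − 1)(1 − q²) / [1 + k² − 2rk − q²(1 − rk)²].

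δ is negative whenever rk < 1, the usual case. If b and c have the same sign, the estimate shrinks by the fraction |δ|·c/b. The same holds for a protective measure such as resilience, with both signs reversed.

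With k = 1 and q = 0.5:
- r = 0.5: δ = (−0.5 × 0.75)/(1 − 0.0625) = −0.40
- r = 0.7: δ = (−0.3 × 0.75)/(0.6 − 0.0225) = −0.39

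**Large-sample logistic fits** (n = 400,000, 15.8% event rate, r = 0.5–0.7, q = 0.5, k = 1) agree with the algebra:

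| True b | True c | SAP model returns | Shrinkage |
|---|---|---|---|
| 0.50 | 0 (only change matters) | 0.49–0.51 | about 0% |
| 0.50 | 0.30 | 0.38 | about 25% |
| 0.50 | 0.50 (only post level matters) | 0.29–0.30 | about 40% |
| 0.50 | 1.00 | 0.09–0.10 | about 80% |
| 0 | 0.50 (only baseline matters) | about −0.19 | wrong sign |

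The third row is the post-level case because 0.5·D + 0.5·B = 0.5·post. Adding B to the model recovers the true change coefficient in every scenario.

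**Sensitivity.** For c = b and q = 0.5, the formula gives 60–70% shrinkage at k = 0.8 and 16–25% at k = 1.2 (r = 0.5–0.7). At k = 1 and r = 0.7, raising q from 0 to 0.7 moves δ from −0.50 to about −0.28. Symptom adjustment reduces the bias but does not remove it.

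**Is c = 0 a natural default?** Given S, the total association of baseline with risk is c + b(rk − 1). If c = 0 and b > 0, this is negative: people high in rumination at baseline would be at lower risk, the reverse of what the SAP reports. This does not fix c, because that cohort had no intervention and no effect size is quoted, but it makes c > 0 plausible.

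**At trial size** (1,500 simulated trials of n = 152; non-zero effects 0.60, r = 0.7, q = 0 or 0.5, rates 8.7% and 15.8%):

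| Truth | Result counted | SAP model | With baseline added |
|---|---|---|---|
| Only post level matters | significant, right direction | 11–19% | 28–44% |
| Only change matters | significant, right direction | 32–49% | 28–44% |
| Only baseline matters | significant, wrong direction | 6–14% | 2–3% (nominal 2.5%) |

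**The case against.** The SAP's hypothesis is about change. If change alone drives risk, the model as written is unbiased and the extra covariate costs about 4–5 points of power. That stands, and it makes the bias conditional.

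The baseline symptom covariate already absorbs part of any baseline effect. That also stands, but only in part.

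The analysis is tertiary, uses one arm and is observational. With roughly 13 or 24 events, power stays below 50% in these scenarios under either model. This stands too and limits the importance of the point.

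A reader might go further and infer that the plan shrinks real change effects by 40–80% as a matter of course, with 40% lost even when baseline has no effect of its own. The documents do not support that, because they give no correlation, SD ratio or effect size for any process measure. The 40% figure arises when the truth is written as an effect of post level with no further baseline term. In the change-plus-baseline model, that is a baseline effect already equal to the change effect. The 80% figure needs it to be double.

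**Conclusion.** The point holds in conditional form. Both SAP sections omit the process measure's baseline level, and the sponsor's own evidence makes an independent baseline effect plausible for rumination and resilience. The change coefficient is then biased toward zero or the wrong sign, by an amount set by the ratio of baseline effect to change effect. The range of about 0% to 80% assumes equal pre and post SDs, r of 0.5–0.7, a process–symptom correlation of 0.5 and a baseline effect between zero and twice the change effect. A different SD ratio moves it either way. The direction needs only rk < 1 and a baseline effect pointing the same way as the expected change effect. Primary and secondary comparisons and the total of 570 are untouched. It is a cheap improvement to a tertiary analysis.

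**What to change.** In the SAP's Statistical Analysis Outline and in Analysis Methods (tertiary objectives), add the baseline score of the same process measure to each logistic regression and keep the baseline PTSD or MDD symptom score. Entering the 6-week score with its own baseline score is equivalent: the coefficient on the 6-week score equals the change coefficient.

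No new data are needed. Protocol Appendix B schedules the RRS brooding subscale, RIQ, intrusion items, concrete and abstract thinking, CD-RISC and Wagnild scales at both baseline and 6 weeks. The cost is a sentence in each place, one more covariate in models with few events, and about 4–5 points of power if change alone matters.
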